    # Calculate the z-scores for the given alpha and power
    z_alpha = norm.ppf(1 - alpha / 2)
    z_power = norm.ppf(power)
    # Compute the required number of events using Schoenfeld's formula
    d = ((z_alpha + z_power) ** 2) / (p * (1 - p) * (math.log(hr)) ** 2)
    # Total sample size adjusted by the expected event rate
    n = d / event_rate
    # Return the sample size rounded up to the next integer
    return math.ceil(n)

# Use ggplot style for the plot
plt.style.use('ggplot')
# Define fixed parameters
alpha = 0.05          # Significance level
p = 0.3               # Proportion in the designated group
event_rate = 0.25     # Expected event rate during follow-up
# Create an array of hazard ratios ranging from 1.4 to 2.0
hr_values = np.linspace(1.4, 2.0, 100)
# Define multiple power values for comparison
power_values = [0.8, 0.85, 0.9]
# Plotting the relationship between hazard ratio and required sample size for different power val-
ues
plt.figure(figsize=(6, 6))
# Draw a horizontal line at sample size = 700
plt.axhline(y=700, color='red', linestyle='--', linewidth=2, label='700 People')
# Draw a vertical line at HR = exp(0.5) ≈ 1.65
plt.axvline(x=1.65, color='blue', linestyle='--', linewidth=2, label='exp(0.5)')
res=[]
for power in power_values:
    sample_sizes = [calculate_sample_size_cox(alpha, power, hr, p, event_rate) for hr in hr_val-
ues]
    plt.plot(hr_values, sample_sizes, linewidth=2, label=f'Power = {power}')
    res_s=pd.DataFrame({'HR': hr_values, 'Sample Size': sample_sizes})
    res_s['Power']=power
    res.append(res_s)
plt.xlabel('Hazard Ratio (HR)')
plt.ylabel('Required Total Sample Size')
plt.title('Sample Size vs Hazard Ratio for Cox PH Model')
plt.legend(title='Statistical Power')
plt.grid(True)
plt.show()
res=pd.concat(res)
res.to_csv('sample_size_vs_hr.csv', index=False)

```

[figure not shown]

**Sample Size vs. Hazard Ratio for Cox Proportional Hazards Model.** The plot displays curves of the required total sample size for detecting a given hazard ratio (HR) under different statistical power settings (80%, 85%, and 90%) using the Schoenfeld formula. The horizontal red dashed line represents a total sample size of 700 subjects, while the vertical blue dashed line marks a hazard ratio of approximately 1.65 (equivalent to  $\exp(0.5)$ ).

## 8.2 Sample Size Estimation for Predictive Model Construction

In developing our predictive model based on the Cox proportional hazards framework, we employed two complementary approaches for sample size determination: Riley’s method and the traditional EPV (events per variable) rule. These methods were used to ensure the robustness of the model while minimizing the risk of overfitting.

### Riley’s Method

Riley’s method is an advanced approach that calculates the required sample size by considering model performance parameters and anticipated shrinkage. Using the R package *pmsampsize*, we computed the required total sample size for a range of candidate predictor numbers (denoted by  $k$ ). The calculations incorporated the following parameters:

- A candidate model’s anticipated performance was characterized by a global  $R^2$ , which was derived using the formula:

$$R_{CS}^2 = \frac{(R_{app} - 0.5)^2}{0.75}$$

where  $R_{app}$  represents the apparent  $R^2$  (in our case, 0.88).

- An expected event rate of 25% was assumed.

- A time horizon of 10 years for the outcome and a mean follow-up of 10 years were specified.

For each value of  $k$ , Riley's method provided an estimate of the required total sample size to achieve a pre-specified level of predictive performance while controlling for overfitting. These estimates were then compared across values of  $k$ .

### EPV-Based Sample Size Calculation

In parallel, we applied the widely used rule-of-thumb based on the events per variable (EPV) criterion. According to this approach, a minimum number of events per predictor is required to reliably estimate model parameters. The required number of events  $D$  is given by:

$$D = EPV \times k$$

where EPV is typically set to 10 (or adjusted to 11 or 12 in sensitivity analyses) and  $k$  represents the number of candidate predictors. Given an expected event rate (denoted as  $\lambda$ ), the total required sample size  $N$  is then calculated as:

$$N = \frac{D}{\lambda} = \frac{(EPV \times k)}{\lambda}$$

For example, assuming an event rate of 25%, the total sample size for an EPV of 10 would be computed as:

$$N = \frac{10 \times k}{0.25}$$

This calculation was performed across a range of  $k$  values, and similar computations were repeated for EPV values of 11 and 12 to assess the sensitivity of the sample size requirement (Figure 2).

In our study, we assumed:

- an expected event rate of 25% (i.e., 0.25),
- candidate predictor numbers ranging up to 15, and
- performance parameters as specified by the global  $R^2$ , where  $R_{app}$  equal to 0.88

The required total sample sizes were:

- EPV = 10: sample size = 640,
- EPV = 11: sample size = 704,
- EPV = 12: sample size = 768.
- Riley's method sample size = 782

Based on these estimates, we ultimately adopted a sample size of 700 participants. This choice is consistent with our initial sample size estimation for protein screening and is expected to provide sufficient power for robust predictive modeling while minimizing the risk of overfitting. The pseudo code is as follows:

```

import math
import numpy as np
import pandas as pd
import matplotlib.pyplot as plt
#####

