#### 3.2 Penn Medicine BioBank (Primary Cohort)

PMBB is an EHR-linked biobank at the University of Pennsylvania with >40,000 participants, ~30% non-European ancestry. We will identify all African-American PMBB participants with APOL1 high-risk genotype (two risk alleles: G1/G1, G2/G2, or G1/G2), age ≥18, and baseline eGFR >60 mL/min/1.73m^2. APOL1 genotype was determined via whole-exome sequencing (Regeneron) or equivalent genotyping. Plasma proteomic profiles (7,549 proteins) were measured at baseline using the SomaScan aptamer platform. We have identified 1,113 eligible participants for the primary cohort (expanded from 550 in the prior dataset). Additional CKD participants with APOL1 high-risk genotype and 967 African ancestry APOL1 low-risk participants (267 newly added) and 698 European ancestry APOL1 low-risk were included as external reference. Baseline covariates include age, sex, eGFR (CKD-EPI 2021), and albumin-to-creatinine ratio (UACR). To better enable comparison between the African ancestry APOL1 high-risk and low-risk groups, propensity score matching was applied using age, sex, eGFR, UACR, diabetes, hypertension, and cardiovascular disease, with separate matching performed for participants with eGFR >60 and ≤60 mL/min/1.73 m^2 (Appendix 1 to 3).

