### **6.4.2 Regularized Cox Regression:**

We will perform a regularized Cox Regression where the L1/L2 ratio varies from 0 to 1. An alpha grid is automatically generated by sklearn and sksurv using 8-fold cross-validation, and the optimal alpha is selected based on the minimization of the partial likelihood deviance. Specifically, for a given L1 ratio, the model will be fitted using CoxnetSurvivalAnalysis (with an alpha\_min\_ratio set to 0.00001 and a maximum iteration of 1000), and a subset of alpha values is extracted for tuning. At each iteration we randomly sampled (with replacement) protein subsets drawn from the top 20% of proteins ranked by univariate AUC and fit the model on those subsets. This procedure was repeated across approximately 1 million different protein combinations.

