# Plot everything: multiple EPV lines (no markers) plus the Riley line
plt.style.use("ggplot")
plt.figure(figsize=(6, 6))
plt.plot(k_values_riley,sample_sizes_riley,linewidth=2,marker=None, label="Riley's Method")
plt.plot(k_values_riley,sample_sizes_epv_10,linewidth=2,marker=None, label="EPV=10")
plt.plot(k_values_riley,sample_sizes_epv_11,linewidth=2,marker=None, label="EPV=11")
plt.plot(k_values_riley,sample_sizes_epv_12,linewidth=2,marker=None, label="EPV=12")
plt.axhline(y=700, color='red', linestyle='--', linewidth=2, label='700 People')
plt.axvline(x=15, color='blue', linestyle='--', linewidth=2, label='15 markers')
plt.xlabel("Number of Candidate Predictors (k)")
plt.ylabel("Required Total Sample Size")
plt.title("Sample Size Estimation: Riley's Method vs. EPV Rule")
plt.legend(title="Method")
plt.grid(True)
plt.show()

```

[figure not shown]

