### Sample Size Estimation Using Riley's Method and the EPV Rule.

The figure illustrates the required total sample size for predictive modeling as a function of the number of candidate predictors ( $k$ ), estimated using both Riley's method (solid red line) and the EPV rule with different assumptions ( $EPV = 10, 11$ , and  $12$ , represented by solid black, blue, and green lines, respectively). Riley's method accounts for model performance characteristics and expected shrinkage, while the EPV rule provides a heuristic estimation based on the number of events per variable. The dashed red horizontal line indicates a reference sample size of 700 participants, and the dashed blue vertical line corresponds to a scenario with 17 candidate predictors. These reference lines aid in visualizing feasible study designs under different methodological assumptions.

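### SAP 8.2 sizes the model on about 15 candidate predictors, but the plan ranks and searches far more, so its overfitting assurance for 700 participants is unsupported; the stated sizes also do not match k = 15.

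*Combined protocol and SAP*

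**What the plan says.** SAP 8.2 uses two methods, the EPV rule and Riley's method. In both, k "represents the number of candidate predictors". The stated assumptions are a 25% event rate, "candidate predictor numbers ranging up to 15", and an apparent performance value of 0.88. The listed requirements are 640, 704 and 768 for EPV of 10, 11 and 12, and 782 for Riley. The SAP adopts 700 and says that this number "is expected to provide sufficient power for robust predictive modeling while minimizing the risk of overfitting".

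The size of the selection problem is described elsewhere. Protocol 3.2: "Plasma proteomic profiles (7,549 proteins) were measured at baseline using the SomaScan aptamer platform". SAP 6.4.2 samples subsets "drawn from the top 20% of proteins ranked by univariate AUC and fit the model on those subsets" and repeats this over about one million protein combinations. Protocol 3.7 gives the finished model as nine proteins plus four clinical covariates, 13 terms in all. Section 8.2 mentions neither the ranking nor the search.

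**The concern.** EPV and Riley's method address overfitting only when k counts every predictor that had a chance to enter the model. The SAP adopts that definition of k, then inserts a number close to the size of the model left after selection. If the outcome has already been used to rank thousands of proteins and to compare a million subsets, most of the optimism comes from that step, and a calculation at k = 15 does not see it.

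At stake is how the PMBB performance figures are read. Someone relying on 8.2 would believe that the sample size itself guards against an over-optimistic C-index or time-dependent AUC. It does not guard against optimism from selection.

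**Working it through.** **Inputs.** EPV rule and 25% event rate: SAP 8.2. Cox-Snell R² = (0.88 − 0.5)²/0.75 = 0.1925: SAP 8.2 text and code. Target shrinkage S = 0.9: an assumption, since the SAP does not state it. Proteins measured: 7,549 (protocol 3.2). Events: 153 of 851 in the derivation set (SAP 3) and 121 of 680 in training (Supplementary Table 1).

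**1. The plan's own figures.** The EPV rule is N = EPV × k / 0.25. Riley's shrinkage criterion, the binding one here, is N = k / [(S − 1) ln(1 − R²/S)].

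| | k = 15 | k = 16 | k = 17 | SAP states |
|---|---|---|---|---|
| EPV 10 | 600 | 640 | 680 | 640 |
| EPV 11 | 660 | 704 | 748 | 704 |
| EPV 12 | 720 | 768 | 816 | 768 |
| Riley | 624 | 665 | 707 | 782 |

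The three EPV figures match k = 16 exactly. The text says up to 15, the plotting code draws its line at 15, and the caption says the line "corresponds to a scenario with 17 candidate predictors". Riley's 782 corresponds to k of about 18.8 (k = 18 gives 748, k = 19 gives 790), which the SAP states nowhere. The Riley code also uses a rate of 0.24 where the text says 25%, and the SAP does not say whether this is cumulative or per year. The binding criterion does not use the rate, so this does not explain 782.

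**2. The adopted number.** 700 exceeds 640 but is below 704, 768 and 782, three of the SAP's four requirements.

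**3. Events per variable with k small.** The plan expected 700 × 0.25 = 175 events, and 175/15 = 11.7. The training set has 121 events: 121/15 = 8.1, 121/16 = 7.6, and 121/13 = 9.3 for the finished model. At the observed event rate (153/851 = 17.98%), EPV 10 with k = 15 needs 150/0.1798, or about 835 participants.

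**4. Events per candidate with k as the SAP defines it.** The search pool is 0.20 × 7,549 = 1,509.8, about 1,510. The SAP does not state the base of the 20%, and SAP 6.1 drops variables with more than 15% missing, so 1,510 assumes that all 7,549 are ranked. Then 121/1,510 = 0.08 and 153/1,510 = 0.10. Against all 7,549, 121 events give 0.016. Putting k = 1,510 into the SAP's formulas gives 10 × 1,510/0.25 = 60,400 (EPV) and 62,733 (Riley).

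**5. Illustration of selection optimism.** Pure-noise proteins were simulated with about 680 people and 121 to 127 events, 40 runs per setting. Apparent C was about 0.57 to 0.58 for nine proteins fixed in advance. It was 0.71 to 0.72 for the top nine of 1,510 independent proteins, and 0.65 to 0.67 when the proteins shared a correlation of 0.3. The true value is 0.50. Scored in 171 held-out people, the same noise models gave mean C of about 0.48 to 0.51. Apparent performance is inflated by selection, and data untouched by selection reveal it. This picks proteins by univariate Cox score and refits without a penalty; it does not replicate the plan's search.

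**The case against.** The strongest reply is that the plan does not depend on 8.2. It specifies a penalised Cox model tuned by cross-validation, an 80/20 split, bootstrap checks of feature stability, and external validation in ARIC (314 high-risk participants) and UK Biobank (204), with coefficients fixed beforehand. Three of the nine proteins also show associations in CRIC (Supplementary Table 2), so pure noise is a worst case. The cohort is retrospective and already fixed at 851, so no enrolment decision turns on 8.2.

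Much of this stands. A reader might infer that the study needs about 60,000 participants. The documents do not support that: EPV and Riley's shrinkage criterion concern unpenalised estimation of all k coefficients, and the plan does not fit such a model. The large-k values show only that the rules do not apply here. A reader might also infer that the APRS is known to be overfitted, or that nothing in the plan guards against overfitting. That does not follow either, given the safeguards above. ARIC in particular plays no part in the described search.

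What does not stand is any defence of the assurance itself. Section 8.2 draws its conclusion from the EPV and Riley figures, not from penalisation or validation. The penalty is tuned within each sampled subset and does not correct for the outcome-based ranking or for taking the best of about a million fits. The bootstraps described cover feature stability, imputation and NNT intervals, not performance optimism. The internal split is weakened because SAP 6.4.3 identifies the best model by deviance within the testing set. That is a separate defect; here it matters only because the PMBB test set cannot be assumed clean.

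**Conclusion.** The concern holds in limited form. By the SAP's own definition of k, the calculation leaves out about 99% of the searched candidates (15 of about 1,510), so the claim that 700 participants minimise overfitting is unsupported. With 121 training events there are about 0.08 events per searched candidate, and 8.1 per variable even at k = 15. Separately, the calculation is internally inconsistent: k is 15, 16 or 17 depending on where one looks, 782 matches none of these, and 700 misses three of four listed requirements.

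The conclusion rests on two assumptions: that the top 20% is taken from all 7,549 proteins, and, for the Riley figures, that target shrinkage is 0.9. A smaller base would lower 1,510 but would not bring it near 15 unless almost all proteins were excluded first. Severity: should be fixed. The correction changes a stated property and the labelling of performance, not the cohort, endpoint or external validation.

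**What to change.** In SAP 8.2:
- State that the EPV and Riley figures apply only to estimating the coefficients of an already locked panel.
- Report the candidates as 7,549 screened and about 1,510 searched, plus four clinical covariates, and state the base of the 20%.
- Delete the overfitting assurance.
- Settle on one k across text, code and caption, recompute the four sizes, reconcile 0.24 with 25%, state the shrinkage target, and say plainly how 700 relates to the corrected requirements.

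For performance, base claims on data not used in selection: ARIC and UK Biobank with locked coefficients, and the PMBB test set only if it plays no part in choosing the model. Label any PMBB training-set C or time-dependent AUC as apparent, unless it is optimism-corrected by resampling that repeats the ranking and a computationally reduced version of the search in every resample. Repeating the full million-combination search each time is not a realistic request. Uniform shrinkage of the coefficients is optional: it affects calibration and leaves C and time-dependent AUC unchanged.

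The cost is redrafting, modest computing time if the reduced resampling is done, and a less favourable sample-size justification. No new participants are needed.

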### 8.1 Sample size for screening the proteins

Sample size estimation for screening the proteins base the Cox proportional hazards model was performed using the Schoenfeld formula. The required number of events  $D$  is given by:

$$D = \frac{(z_{1-\alpha/2} + z_{1-\beta})^2}{p(1-p)[\ln(HR)]^2},$$

where:

- $\alpha$  is the two-sided significance level (set to 0.05, so that  $z_{1-\alpha/2} \approx 1.96$  ).
- $\beta$  is the Type II error rate (with statistical power =  $1 - \beta$ ).
- $p$  is the expected proportion of subjects who with marker-positive (in this study, 30% or  $p = 0.3$ ).
- $\ln(HR)$  is the natural logarithm of the hazard ratio to be detected.

The total sample size  $N$  is then calculated by adjusting the required number of events by the expected event rate during follow-up:  $N = \frac{D}{\text{event rate}}$

In our study, we assumed:

- an expected event rate of 25% (i.e., 0.25),
- an anticipated hazard ratio of approximately 1.648 (which is close to  $\exp(0.5)$ ).

Under these assumptions, enrolling 685 subjects would yield an effective statistical power of about 85% for detecting a hazard ratio of 1.648 (Figure 1). The pseudo code is as follows:

```

import math
import numpy as np
import matplotlib.pyplot as plt
from scipy.stats import norm
import pandas as pd
def calculate_sample_size_cox(alpha, power, hr, p=0.5, event_rate=1.0):
    """
    Calculate the required sample size for a Cox proportional hazards model
    based on the Schoenfeld formula.
    Parameters:
        alpha (float): Significance level (Type I error rate), e.g., 0.05.
        power (float): Statistical power (1 - beta), e.g., 0.8.
        hr (float): Hazard ratio to detect, e.g., 1.65.
        p (float): Proportion of subjects in the designated group (default is 0.5).
        event_rate (float): Expected event rate during the study period (default is 1.0, meaning
all subjects experience the event).
    Returns:
        n (int): Estimated total sample size required.
    """

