  # Call pmsampsize with the current parameter and store the result in res
  res <- pmsampsize(type = "s", csrsquared = (0.88 - 0.5)^2 / 0.75, parameters = i,
    rate = 0.24,timepoint = 10, meanfup = 10)

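### SAP 8.2: the Riley sample size of 782 comes from entering a 25% event proportion as a yearly rate; corrected, it is 624, 665 or 707 for 15, 16 or 17 predictors

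*Combined protocol and SAP*

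**What the plan says.** SAP 8.2 (Riley's Method) states: "An expected event rate of 25% was assumed". It adds: "A time horizon of 10 years for the outcome and a mean follow-up of 10 years were specified". A Cox-Snell R² is derived from 0.88, which the text calls an apparent R². The printed R call has "csrsquared = (0.88 - 0.5)^2 / 0.75, parameters = i" and "rate = 0.24,timepoint = 10, meanfup = 10". The assumptions listed after the EPV rule include "candidate predictor numbers ranging up to 15, and". The results given are 640, 704 and 768 for 10, 11 and 12 events per variable, and "method sample size = 782" for Riley. The SAP then adopts 700 participants on the strength of these estimates and notes that this agrees with the protein-screening calculation.

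Elsewhere in section 8 the same 25% is a share of participants. SAP 8.1 obtains the total by "adjusting the required number of events by the expected event rate during follow-up". The EPV rule divides by 0.25 in the same way: "assuming an event rate of 25%, the total sample size for an EPV of 10 would be computed as" 10 × k / 0.25.

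**The concern.** In Riley's criteria for a survival outcome, the expected number of events per person is the event rate multiplied by mean follow-up, so the rate must be per unit of time. The SAP's 25% is a proportion over the whole follow-up. Paired with a mean follow-up of 10 years, it gives 2.5 events per person (2.4 with the code's 0.24). Protocol 3.6 defines the endpoint as the earliest of its components, so nobody can contribute more than one event.

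The Riley calculation is one of two that SAP 8.2 offers as protection against overfitting. As printed, the SAP adopts 700 below its own Riley requirement of 782 and does not comment on the gap. A reader cannot tell whether that shortfall is real.

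**Working it through.** **Inputs**
- R² = (0.88 − 0.5)² / 0.75 = 0.1925 (SAP 8.2, text and code).
- Event rate 0.25 (text) or 0.24 (code); mean follow-up and horizon 10 years (both).
- Number of predictors k = 15 (text, and the reference line in the plotting code). The EPV results imply 16: 640 × 0.25 / 10 = 16, 704 × 0.25 / 11 = 16, 768 × 0.25 / 12 = 16. The figure legend says 17.
- Assumed, because the call sets neither: target shrinkage 0.9 and margins of 0.05, taken as the package defaults.

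**Formulas**, with e = rate × mean follow-up
- Criterion 1 (shrinkage): n = k / [(S − 1) ln(1 − R²/S)], S = 0.9.
- Criterion 2 (optimism in R²): the same expression with S = R² / (R² + 0.05 × max R²), where max R² = 1 − exp[2(e ln e − e)].
- Criterion 3: overall 10-year risk estimated to within 0.05.
- The requirement is the largest of the three, rounded up.

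**Reproducing 782** (k = 15, rate 0.25, e = 2.5)
- Criterion 1: ln(1 − 0.1925/0.9) = −0.2407; n = 15 / (0.1 × 0.2407) = 623.2, so 624.
- Criterion 2: e ln e − e = −0.2093; max R² = 1 − exp(−0.4185) = 0.342; S = 0.9184; n = 781.65, so 782.
- Criterion 3: 43.
- Requirement 782, an exact match. Criterion 2 governs only because the impossible event count pushes max R² down to 0.342.

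**The printed code** (k = 15, rate 0.24, e = 2.4): max R² = 0.450; criterion 2 gives 593; criterion 1 gives 624. The code therefore returns 624. With rate 0.24, no k from 13 to 20 gives 782; the nearest is 790 at k = 19. With rate 0.25, k = 16 gives 834 and k = 17 gives 886. Among the rates and predictor counts the SAP supplies, only 0.25 with k = 15 yields the printed number.

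**Corrected** (25% as a 10-year proportion: 0.025 per year × 10 years, e = 0.25)

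| k | Criterion 1 | Criterion 2 | Criterion 3 | Requirement |
|---|---|---|---|---|
| 15 | 624 | 380 | 249 | 624 |
| 16 | 665 | 405 | 249 | 665 |
| 17 | 707 | 431 | 249 | 707 |

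Here max R² = 0.697. Criterion 1 governs and contains neither the rate nor the follow-up. At k = 15 the answer stays at 624 with 0.024 per year, with −ln(0.75)/10 = 0.0288 per year, and with the observed proportion of 153/851 = 0.180, whether mean follow-up is set at 6.51, 7.18 or 10 years. A 10-year mean cannot realistically be reached under a 10-year cap (Protocol Appendix 1 shows 7.18), but this does not move the corrected number.

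**What does move it** is 0.88. The formula subtracts 0.5, the value of a C-statistic with no discrimination; an R² has no such reference point. Applying the SAP's own conversion at k = 15 to assumed C values, which are not in the documents:

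| Assumed C | R² | Requirement |
|---|---|---|
| 0.88 (SAP input) | 0.1925 | 624 |
| 0.85 | 0.1633 | 750 |
| 0.80 | 0.1200 | 1,049 |
| 0.75 | 0.0833 | 1,544 |

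On this scale 851 participants suffice for C of about 0.83 or more, and the 680 in training for about 0.87 or more.

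**The case against.** The best defence is that the error is conservative and did not set the sample size. The SAP adopted 700 although 782 was larger, and it ties 700 to the screening calculation. On the SAP's own inputs at k = 15, the adopted 700, the training set of 680 and the derivation set of 851 all exceed 624. The study is a retrospective cohort with 851 participants and 153 events already fixed, so no recruitment decision changes. All of this stands. It limits the consequence but does not make 782 correct.

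A reader might infer that the adequacy statement fails whichever way the figure is corrected: too high as printed, too low once discrimination is set lower. The documents do not support that. They give no C-statistic other than 0.88, the lower values above are assumptions, and even at 0.85 the requirement of 750 is below 851. The sensitivity table also takes the SAP's conversion to R² as given.

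It can also be said that the 0.24 sits in what the SAP labels pseudocode. That may explain the mismatch with 25%, but the two still have to agree. Finally, SAP 6.4.2 searches about one million protein combinations drawn from the top fifth of the measured proteins, so a calculation at k = 15 to 17 does not capture the full selection process. That is fair, and it means the corrected number should not be presented as proof against overfitting.

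**Conclusion.** The printed 782 is wrong. It follows from using a cumulative proportion as a yearly rate, and the SAP's own code does not return it. With the unit corrected and the package defaults assumed, the requirement is 624 at k = 15, 665 at k = 16 and 707 at k = 17.

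The printed figure therefore exceeds the corrected one by 158, 117 or 75. At k = 15 or 16 the apparent shortfall of 700 disappears; at k = 17 a shortfall of 7 remains. No single replacement can be named until the SAP settles k. Whether 700, 680 or 851 is enough is conditional on discrimination near the 0.88 that was entered. The exact match to 782 supports the diagnosis and the assumed defaults.

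**What to change.** In SAP 8.2:
- Rerun the Riley calculation with a per-year rate and a mean follow-up on the same basis. Either use 0.025 × 10 years, or use the observed 153 events with one person-time denominator throughout: 153 / (851 × 6.51) = 0.0276 per year goes with 6.51 years, not with 7.18.
- Settle k and use it in the text, EPV results, code and legend, which now point to 15, 16, 15 and 17.
- Replace 782 with the resulting figure, and make the rate in the text and code agree.
- Relabel 0.88 as a C-statistic, say where it comes from and whether it is corrected for optimism.
- State the shrinkage target and margins used.
- Optionally, add the sensitivity table with its C values marked as assumptions, and say for which of them 700, 680 and 851 are sufficient.

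The cost is one rerun and a few lines of text. No data, participant numbers or analyses change.
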